## Methods and analysis

2

### Study design, participants, and procedure

2.1

This study is an addition to the NCT05186337 clinical trial. We will conduct a prospective longitudinal observational MRI study. We will invite older adult patients diagnosed with BD type I or II who are about to receive FROA-BD at the Bipolar and Depressive Disorder Unit at the Hospital Clinic of Barcelona to participate. The sample will comprise at least 32 patients (50% males and 50% females). Inclusion criteria will include: (a) aged 60 or over; (b) diagnosis of BD type I or type II according to the Diagnostic and Statistical Manual of Mental Disorders (DSM-5) (35); (c) full or partial remission at the time of assessment, defined as scores ≤14 on the Hamilton Assessment of Depression Scale (HDRS) (36, 37) and ≤ 10 on the Young Mania Rating Scale (YMRS) (38, 39); (d) presence of functional impairment defined as a total score ≥ 11 on the FAST (40); and (e) written informed consent to participate in the study. Exclusion criteria will include: (a) estimated intelligence quotient (IQ) lower than 85; (b) having received a structured psychological intervention within the last 6 months; (c) presenting any central nervous system condition, other than mental disorders, that may affect neuropsychological performance or any physical condition that may hamper participation or assimilation of the contents of the intervention (e.g., severe visual or hearing impairment); (d) presence of any current comorbid psychiatric condition; (e) history of cranioencephalic trauma; and (f) having received electroconvulsive therapy 6 months before the inclusion study.

After consenting, participants will undergo a demographic, clinical, functional, and neuropsychological assessment and an MRI session. Afterward, patients will receive the 32 sessions of FROA-BD throughout 4 months while continuing their usual pharmacological treatment. Finally, after finishing the FROA-BD, patients will undergo a second clinical, functional, and neuropsychological assessment and a second MRI session. For more details on the FROA-BD protocol and program description, see Montejo et al. (20).

Discontinuation criteria will include (a) withdrawal of consent by the participant; (b) significant clinical relapse or hospitalization for any episode; and (c) not attending more than eight sessions during the intervention.

### Sample size estimation

2.2

We aim to include 28 participants because previous studies with 23–28 participants found effects (29–31). In addition, with this sample size, we would have ~80% power to detect moderate correlations (r 0.56) after correcting for multiple testing (correlations in three ROIs: left dorsolateral, bilateral dorsomedial, and right dorsolateral prefrontal cortices). Note that this sample size does not include those patients who, even if consenting to participate, leave the study before finishing the baseline assessment and MRI acquisition.

As we anticipate the possibility of participant attrition during the follow-up, we plan to enroll 32 participants (i.e., ~15% more) to counteract the potential dropouts.

### Clinical and neuropsychological assessment

2.3

We will use a semistructured clinical interview based on the SCID-5 (41) complemented with a revision of medical records to assess baseline demographic and clinical variables. To assess clinical symptomatology, functional outcome, cognitive reserve, quality of life and well-being, and medical comorbidity, we will use the HDRS, the YMRS, and other standard scales shown in Table 1. A trained neuropsychologist will then administer a comprehensive neuropsychological battery of tests to evaluate the following cognitive domains: attention, processing speed, working memory, verbal learning and memory, visual memory, executive functions, language, and visuospatial skills (Table 1). The selected instruments are considered reliable tools to assess cognition in BD, and they are included in the consensus proposed by the International Society for Bipolar Disorders (ISBD) (42). Moreover, the cognitive assessment will also include two cognitive screening instruments [the Minimental Status Examination (MMSE) (43) and the Spanish version of the Screen for Cognitive Impairment in Psychiatry (SCIP-S) (44, 45)], and a scale for gathering subjective cognitive complaints [the Cognitive Complaints in Bipolar Disorder Rating Assessment (COBRA) (46)].

**Table 1 tab1:** Clinical and cognitive measurements at baseline and post-treatment.

		Baseline	Post-treatment
Clinical symptomatology	HDRS		
	YMRS		
Medical comorbidity	CIRS-G		
Psychosocial Functioning	FAST		
Well-being and quality of life	SF-36		
	WHO-5		
Cognitive reserve	CRASH		
Cognition	MMSE		
	SCIP-S		
	Vocabulary (WAIS-III)		
	Arithmetic (WAIS-III)		
	Symbol Search (WAIS-III)		
	Digit-Symbol coding (WAIS-III)		
	Digits (WAIS-III)		
	Letter-Number Sequencing (WAIS-III)		
	WSCT		
	SCWT		
	ROCF		
	CPT-II		
	TMT-A		
	TMT-B		
	CVLT		
	F-A-S (COWAT)		
	Animal Naming (COWAT)		
	Boston Naming Test		
	Juice Line Orientation-form H		
	COBRA		

CIRS-G, Cumulative Illness Rating Scale-Geriatrics; COBRA, Cognitive Complaints in Bipolar Disorder Rating Assessment; COWAT, Controlled Oral Word Association Test; CPT, Continuous Performance Test; CRASH, Cognitive Reserve Assessment Scale in Health; CVLT, California Verbal Learning test; FAST, Functional Assessment Short Test; fMRI, Functional Magnetic Resonance Imaging; HDRS, Hamilton Depression Rating Scale; MRI, Magnetic Resonance Imaging; MMSE, Mini-Mental State Examination; ROCF, Rey Osterrieth Copy figure; SCIP, Screen for Cognitive Impairment in Psychiatry; SCWT, Stroop Color Word Test; TMT-A, Trail Making Test part A; TMT-B, Trail Making Test part B; YMRS, Young Mania Rating Scale; WAIS-III, Wechsler Adults Intelligence Scale 3rd edition; WCST, Wisconsin Card Sorting Test; WHO-5, World Health Organization-Five Well-Being Index. Color shading means when the clinical and cognitive measurements at baseline and post-treatment are administered.

The post-intervention assessment will be briefer (Table 1), comprising the assessment of clinical and functional outcomes, quality of life, and subjective cognitive complaints, but a substantially brief neuropsychological assessment. The latter will only include the alternative form of the cognitive screening tool (SCIP) (45) and a few tests to assess attention and executive functions to avoid potential learning effects, given the short period between baseline and post-intervention assessment. For more details about all the assessment tests, see Table 1.

### Intervention description

2.4

The FROA-BD program consists of a group intervention (approximately eight participants per group) with 90-min sessions twice weekly for 16 weeks. It aims to improve psychosocial functioning by targeting neurocognitive functions such as attention, memory, executive functions, language, and visuospatial skills. It also addresses healthy lifestyle habits, emotional management, social skills, and training in digital competencies. It includes 30 sessions for patients and two sessions for relatives or caregivers. The sessions provide different kinds of strategies to improve psychosocial functioning, focusing on cognitive training of the different cognitive functions. It is important to highlight that, in the FROA-BD intervention, patients aged 60 or older will be included instead of 50 years old as the ISBD defined OABD population; this is because the original FR program established a cut-off point below 60, therefore, we tried to cover this usually excluded age range from traditional RCTs.

### MRI acquisition and functional tasks

2.5

MRI acquisitions will be conducted on a Siemens Magnetom Prisma Fit 3 T device at Hospital Clínic of Barcelona and will last approximately 45 min. We will instruct participants to remain still and place pads around their heads to minimize head movement.

The MRI acquisition protocol will include a high-resolution T1-weighted structural Three-dimensional Magnetization-Prepared Rapid Acquisition with Gradient Echo (3D-MPRAGE) sequence (repetition time (TR) 2,300 ms; echo time (TE) 3 ms; inversion time (TI) 900 ms; flip angle 9°; 240 sagittal slices with 1 mm×0.94 mm×0.94 mm voxel size and 256 × 256 matrix size), a multi-shell DWI sequence (90 diffusion encoding directions and two different phase encoding directions (AP and PA); b-values 1,000, 2000, and 3,000 s/mm^2^; five b0 volumes; TR 5400 ms; TE 113 ms; 100 transverse slices with 1.5 mm isotropic voxel size and 150 × 150 matrix size), a single voxel spectroscopy (SVS) localized in the left dorsomedial prefrontal cortex (with and without water suppression, with 96 and 16 acquired averages, respectively; TR 3000 ms; TE 30 ms; 20x30x15mm voxel size), two gradient-echo echo-planar (EPI) sequences for the cognitive tasks (TR 1500 ms; TE 37 ms; 72 transverse slices with 2 mm isotropic voxel size and 104 × 104 matrix size), and their corresponding gradient field mapping (GFM) to estimate and correct susceptibility artifacts caused by lack of homogeneity in the field. We will inspect the images visually to detect anomalies or artifacts.

#### N-Back paradigm

2.5.1

The sequential-letter version of the n-back working memory task (duration: 8 min 42 s) evaluates two levels of working memory load (1-back and 2-back) in a block-design manner. During the blocks, a projector displays a single letter on the screen every 2 s (1 s on, 1 s off). Each block consists of 24 letters, including five randomly located targets. In the 1-back blocks, the letters are color-coded in green. Participants must detect those that are the same as the one presented just before (e.g., the letter “J” in the sequence “A-K-J-J”). In the 2-back blocks, the letters are color-coded in red. Participants must detect letters that are the same as the one presented before the last (e.g., the letter “K” in the sequence “G-K-O-K”). Participants must indicate targets by pressing a button. Four 1-back and four 2-back blocks are presented interleaved. Between them, the baseline stimulus (an asterisk flashing with the same frequency as the letters) is shown for 16 s. Participants will undergo a training session outside of the scanner before starting.

To measure participants’ performance in the n-back, we will use the signal detection theory index of sensitivity, d′ (47), which separately analyses true and false positives. We will exclude participants with negative d′ values in either or both 1-back and 2-back versions of the task, as negative values suggest that participants are not performing the task effectively.

#### Verbal memory paradigm

2.5.2

The verbal memory task (duration: 9 min 41 s) consists of an audio-adapted version of a well-established neuropsychological test, the Rey Auditory Verbal Learning Test (RAVLT) (48), which evaluates both encoding and retrieval verbal memory. In the control condition, patients passively listen to a list of incomprehensible words, then move onto the encoding phase where they must memorize a list of 15 understandable words. Following a silent period for retrieval, during which the patients must recall as many words as possible, the cycle is repeated. For quality assurance, participants will be asked to recall the words freely when finishing and outside the scanner. Instructions for that task will be given outside the scanner before starting and then just a reminder inside the scanner just before the task begins.

### MRI data preprocessing

2.6

To estimate regional gray and white matter volumes from T1-weighted data, we will apply field bias correction, tissue segmentation, and normalization with SPM12 Segment and template creation and registration with DARTEL (49). We will use both modulated and unmodulated images as they convey complementary volumetric information (50) and apply 8 mm FWHM Gaussian smoothing. To estimate cortical thickness and surface area, we will use FreeSurfer (51) according to ENIGMA pipelines.^1^

To estimate WM tissue properties from DWI data, we will use the last generation BIDS App MRtrix3_connectome (52), which includes DWI denoising (53), Gibbs-ringing removal (54), geometric unwarping distortion corrections using TOPUP (55), eddy current and motion correction (56) and bias field correction (57). We will then use FSL “dtifit” to calculate the fractional anisotropy (FA), axial diffusivity, radial diffusivity, and mean diffusivity; we will also estimate microstructural diffusivity (58). For FA, we will establish a study-specific template by registering the FA images of all subjects to a common space and generating the mean FA skeleton, then project individual FA maps onto it and conduct Tract-Based Spatial Statistics (TBSS) (59, 60). Conversely, we will conduct voxel-based analyses for other diffusivity parameters.

Regarding spectroscopy, we will estimate absolute and creatine-corrected metabolite ratios in the volume of interest (VOI) located in the dorsomedial prefrontal cortex using LCModel version 6.3 (61). Previously, after visually confirming the correct positioning of the VOI, the T1-weighted sequences will be segmented with SPM12 (see above), and we will estimate within-voxel water concentration employing the retrieved tissue probability maps. This adjustment allows partial tissue volume correction when estimating the absolute metabolite concentrations. Further, we will fit glutamate, Glx (glutamate + glutamine), myoinositol, N-acetyl aspartate + N-acetyl-aspartyl-glutamate, and glycerophosphocholine + phosphocholine spectral peaks to a basis spectrum for absolute and creatine corrected metabolite quantification employing the unsuppressed water signal to perform eddy current correction. We will exclude metabolite levels showing FWHM (full-width at half-maximum) > = 10 ppm, SNR (signal-to-noise ratio) < 10, or SD (standard deviation of the estimated concentrations of each metabolite) > 15%.

Finally, we will preprocess fMRI data using fMRIPrep (62), which includes motion correction, slice time correction, susceptibility distortion correction using the GFM, 4 mm FWHM Gaussian smoothing, detrending, and high-pass temporal filter with a 128 s cut-off. Following preprocessing, we will conduct the first-level (individual) analysis to obtain activation maps by fitting a GLM to the preprocessed images using the Nilearn toolbox. We will design the model’s regressors to capture changes in the BOLD signal corresponding to each stimulus, convolving task-related temporal representations with the canonical Glover hemodynamic response function. Nuisance regressors derived from fMRIPrep will be incorporated into the design matrix to minimize the residual error. For n-back, we will compute the following contrasts: 1-back vs. baseline, 2-back vs. baseline, and 2-back vs. 1-back. We will compute the following contrasts for verbal memory: recall vs. control, encoding vs. control, and recall + encoding vs. control. Finally, utilizing the anatomical scan, the activation maps will be spatially normalized to a 2 × 2 × 2 mm^3^ MNI template by employing the ANTs registration toolbox in preparation for subsequent second-level analysis.

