### Objectives

1.2

The main objective is to correlate the pre-post changes in the activation of the dorsolateral and dorsomedial prefrontal cortices during the working memory n-back task (2-back vs. baseline) and pre-post changes in psychosocial functioning assessed with the Functioning Assessment Short Test (FAST).

Secondary, explorative objectives are to correlate (a) pre-post changes in MRI data with pre-post changes in cognition and psychosocial functioning outcomes; and (b) baseline MRI data with pre-post changes in cognition and psychosocial functioning outcomes. For the secondary objectives, we plan to conduct comprehensive whole-brain correlation analyses (corrected for multiple testing) and use several MRI modalities (regional tissue volume, cortical thickness, and surface area; fractional anisotropy and diffusivity measures, activation during the working memory n-back task and a verbal memory task; and frontal spectroscopy).

Finally, we will repeat all the analyses on those results that reach statistical significance according to sex to explore potential differences depending on sex.

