### Data analysis

2.7

The primary outcome will be the correlation between pre-post changes in the activation of the dorsolateral and dorsomedial prefrontal cortex during the working memory n-back task (2-back vs. baseline) and pre-post changes in psychosocial functioning assessed with the Functioning Assessment Short Test (FAST) (63). Specifically, we will conduct three correlations: one for the left dorsolateral, one for the bilateral dorsomedial, and one for the right dorsolateral prefrontal cortex. We will use a permutation test to correct for multiple testing (three correlation tests).

For the secondary analyses, we will conduct two kinds of correlations: (a) pre-post changes in MRI data with pre-post changes in cognition and psychosocial functioning outcomes, and (b) baseline MRI data with pre-post changes in cognition and psychosocial functioning outcomes. We will include as covariates the variables from age, sex, bipolar disorder type, medication (use of lithium, antiepileptics, antidepressants, and antipsychotics), illness history (duration of the illness and number of episodes), or educational level that show statistically significant associations with the MRI signal or the cognition/functioning outcome; in case that several variables show statistically significant associations, we will select those still showing statistical significance in multiple regression. We will report results for structural MRI analyses using both familywise error rate (FWER) < 0.05 based on conservative permutation tests (64) and threshold-free cluster enhancement (TFCE) (65) and uncorrected *p* < 0.001 (at the exploratory level). For spectroscopy, we will use linear models. Finally, for fMRI analyses, a paired t-test will be conducted on single-subject contrast to examine temporal changes in activation, employing the Nilearn toolbox. We will break down and localize clusters using SDM ‘imgcalc’ tool (66).

We will also repeat all the analyses on those results that reach statistical significance according to sex to explore potential differences.

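### The T1 processing steps in section 2.6 include no within-subject step, although exploratory objective (a) correlates within-person change in volume, thickness and surface area

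*Protocol article*

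**What the plan says.** Section 1.2 (Objectives) of the Protocol article introduces this part of the study with "Secondary, explorative objectives are to correlate (a) pre-post changes in MRI data". It says the study will "use several MRI modalities (regional tissue volume, cortical thickness, and surface area", alongside diffusion, fMRI and spectroscopy. Section 2.7 repeats the two kinds of correlation. Kind (a) relates "pre-post changes in MRI data with pre-post changes in cognition and psychosocial functioning outcomes"; kind (b) relates "baseline MRI data with pre-post changes in cognition and psychosocial functioning outcomes". By section 2.1, the two scans lie on either side of a four-month programme.

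Section 2.6 (MRI data preprocessing) gives the T1 processing. For volumes it lists bias correction, then "tissue segmentation, and normalization with SPM12 Segment and template creation and registration with DARTEL". It adds: "We will use both modulated and unmodulated images as they convey complementary volumetric information", followed by 8 mm smoothing. For the surface measures it says: "To estimate cortical thickness and surface area, we will use FreeSurfer (51) according to ENIGMA pipelines".

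These are the only T1 steps given, and they serve both the change analyses (a) and the baseline analyses (b). Nothing is said about a within-subject template, registration of a patient's two scans to each other, or a longitudinal processing stream.

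**The concern.** A baseline analysis uses one scan per person. A change analysis uses the difference between two, so it carries the error of both. If each scan is segmented and registered without reference to the other, any error specific to one scan stays in the difference. True structural change over about four months may be small relative to that error, so the change score can be much less reliable than either scan alone.

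At stake is the sensitivity of exploratory objective (a) for the three T1 measures. With 28 analysable patients there is little power to spare. A null structural-change result would be hard to interpret, because it could reflect absence of a relation or noise from processing.

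**Working it through.** **1. The article's own figure.** Section 2.2 states about 80% power for r = 0.56 with 28 participants after correction for three ROI correlations. Alpha and sidedness are not given; I assume 0.05/3, two-sided.

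- Fisher z: power = Φ(atanh(r)·√(n − 3) − z). Here atanh(0.56) = 0.633, √25 = 5 and z = 2.394. So Φ(3.164 − 2.394) = 77.9%.
- Simulation of the test for r under bivariate normality (400,000 runs): 79.2%.

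The stated figure reproduces. It belongs to the primary fMRI analysis, which uses no volume, thickness or area, so nothing below changes it.

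**2. Mechanism.** Let s_true be the SD of true change, s_err the processing-error SD per scan, and ρ the correlation of the two scans' errors.

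- Reliability of change = s_true² / (s_true² + 2·s_err²·(1 − ρ))
- Observed r = true r × √reliability

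Error shared by the scans (ρ near 1) cancels. Error that is not shared remains and attenuates.

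**3. Illustration with assumed SDs.** The article gives none of these values. Take s_true = 0.02 mm for thickness and true r = 0.56.

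- s_err = 0.04 mm, ρ = 0: 0.0004/(0.0004 + 0.0032) = 0.11; observed r = 0.56 × √0.11 = 0.19.
- s_err = 0.02 mm, ρ = 0: 0.0004/(0.0004 + 0.0008) = 0.33; observed r = 0.32.
- s_err = 0.04 mm, ρ = 0.75: 0.0004/(0.0004 + 0.0032 × 0.25) = 0.33; observed r = 0.32.

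The third line shows that the loss depends on how far the errors are shared, as well as on their size.

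**4. The same from single-scan reliability.** Reliability of change = (rel − r12)/(1 − r12), where r12 is the observed correlation between baseline and follow-up. With rel = 0.98 and r12 = 0.95 (both assumed): 0.03/0.05 = 0.60, so r falls from 0.56 to 0.43. A measure that is very reliable on one occasion can still give a mediocre change score.

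**5. Range, at the uncorrected threshold in section 2.7.** n = 28, true r = 0.56, p < 0.001 taken as two-sided, Fisher z:

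| Reliability of change | Observed r | Power at p < 0.001 |
|---|---|---|
| 1.0 | 0.56 | 45% |
| 0.9 | 0.53 | 37% |
| 0.7 | 0.47 | 23% |
| 0.5 | 0.40 | 12% |
| 0.3 | 0.31 | 4% |

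**6. What is not touched.** Error unrelated to the outcome leaves a true zero correlation at zero, so type I error is unchanged. Objective (b) takes no difference between scans.

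**The case against.** The strongest reply is that separate processing is inferred from silence. Section 2.6 names software in two sentences of a condensed article, and those packages also offer longitudinal processing, so the names do not settle which was meant. For thickness and area the article defers to pipelines that are not reproduced. This stands in part: the article never calls the processing cross-sectional. But section 2.6 is not a loose summary. It gives the order of steps, smoothing kernels, a software version, spectroscopy exclusion limits and a filter cut-off. In a list that specific, the listed T1 steps are the plan as it can be read, and none of them links a patient's two scans.

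The second reply is that the errors need not be independent. Section 2.5 fixes one scanner and one sequence, and both scans show the same anatomy, so part of the error may cancel. This stands, and step 3 shows that it matters. It limits the size of the effect but leaves its direction unchanged, because only the unshared part counts.

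The third reply is that sample size and threshold dominate. At n = 28, |r| must reach about 0.59 for two-sided p < 0.001, and power is only 45% even without error. In the illustration, moving r from 0.19 to 0.32 raises power at that threshold only from about 1% to about 5%. This also stands, so better processing should not be presented as a rescue of the analysis.

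Finally, the affected analyses are exploratory. The tentative structural hypothesis in section 1.1 concerns baseline thickness, which falls under objective (b). This stands and sets the severity.

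**Conclusion.** The point holds as a minor one. The T1 steps as listed contain no within-subject step, while objective (a) needs within-person change. Followed literally, they let unshared processing error into the change scores and attenuate the correlations toward zero. The direction rests on one assumption: that some processing error is specific to each scan. The size cannot be computed from the article, and every reliability and SD used above is assumed.

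A reader might infer three stronger things that the document does not support:

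- That the article commits to cross-sectional processing. It does not say so; this is a reading of the listed steps.
- That the structural change analyses would come out null whatever the truth because of the processing. No reliability is given, and 28 patients with p < 0.001 or familywise thresholds already limit power.
- That the main result is weakened. The primary fMRI correlation, its power of about 80%, the type I error and objective (b) are all unaffected.

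**What to change.** For the structural change analyses under objective (a) only, state in section 2.6 and use:

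- for thickness and surface area, the FreeSurfer longitudinal stream, which builds a within-subject template from both scans;
- for regional volumes, SPM12 pairwise longitudinal registration to a within-subject midpoint, before segmentation and DARTEL.

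Keep the listed pipelines for the baseline-only analyses under objective (b). Fix the choice before analysis, so that the stream is not selected after results are seen. If longitudinal processing is already intended, a sentence in section 2.6 naming it for each measure settles the matter.

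The cost is extra computing time and two processing streams to report. No new scans, patients or software packages are needed.

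### The spectroscopy linewidth limit of 10 ppm is wider than the whole metabolite range, so as written this one of three quality checks can exclude no fittable spectrum

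*Protocol article*

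**What the plan says.** Section 2.5 (MRI acquisition and functional tasks) names the scanner, a "Siemens Magnetom Prisma Fit 3 T device", and the acquisition, "a single voxel spectroscopy (SVS) localized in the left dorsomedial prefrontal cortex". Section 2.6 (MRI data preprocessing) describes the quantification: "we will fit glutamate, Glx (glutamate + glutamine), myoinositol, N-acetyl aspartate + N-acetyl-aspartyl-glutamate, and glycerophosphocholine + phosphocholine spectral peaks to a basis spectrum". Metabolites are reported both as absolute values and relative to creatine.

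The same section then gives the exclusion rule. Its first limit is "We will exclude metabolite levels showing FWHM (full-width at half-maximum) > = 10 ppm". The other two follow in the same sentence: "SNR (signal-to-noise ratio) < 10, or SD (standard deviation of the estimated concentrations of each metabolite) > 15" per cent. The three are joined by *or*, so meeting any one is enough to exclude. No other section gives a different linewidth limit.

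Section 2.7 (Data analysis) states how the retained values are used: "For spectroscopy, we will use linear models". Section 1.2 (Objectives) places frontal spectroscopy among the modalities for the secondary, exploratory objectives.

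**The concern.** A linewidth limit is meant to remove spectra whose peaks are too broad to be told apart. It can do so only if it is narrow compared with the spacing of the peaks being fitted. A limit of 10 ppm looks wider than the entire range over which those peaks lie. If so, one of the three stated checks has no effect, and a spectrum that is too broad but otherwise strong is held back only by the other two.

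The quality of the spectroscopy values is at stake. They enter the secondary analyses both as baseline values and as pre-post changes, and a poorly resolved spectrum at either session adds error to the change. Separately, if the limit is found to be unworkable only once spectra are in hand, its replacement would be chosen after the data have been seen.

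**Working it through.** The article derives 10 ppm from no inputs, so there is no calculation of its own to reproduce. The check converts the limit to Hz, compares it with the metabolite range, and asks whether the signal-to-noise limit would stand in for it.

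**Inputs from the article**
- Linewidth limit: FWHM of 10 ppm or more (section 2.6).
- Other limits: signal-to-noise ratio below 10, or SD above 15% (section 2.6).
- Field strength: 3 T (section 2.5).

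**Assumptions (general MR values, not in the article)**
- Proton frequency: 42.577 MHz per tesla, with an actual field of 2.89 to 3.0 T.
- Width of the metabolite range: 4 ppm, varied from 3 to 5 ppm.
- Creatine-choline separation: about 0.17 ppm.
- Good linewidth: 0.04 to 0.06 ppm.
- At fixed peak area, peak height is inversely proportional to FWHM.

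**Step 1. Convert the limit to Hz.** Hz = ppm × proton frequency in MHz.
- 2.89 T: 42.577 × 2.89 = 123.05 MHz, so 10 ppm = 1,230 Hz.
- 3.0 T: 42.577 × 3.0 = 127.73 MHz, so 10 ppm = 1,277 Hz.

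**Step 2. Compare with the metabolite range.**

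| Assumed range | 10 ppm ÷ range |
|---|---|
| 3 ppm | 3.3 |
| 4 ppm | 2.5 |
| 5 ppm | 2.0 |

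Against the assumed creatine-choline gap, 10 ÷ 0.17 is about 59. A line this wide would merge every listed metabolite into one hump, which no fit could resolve. The criterion therefore excludes nothing, wherever in the 3 to 5 ppm span the true range lies.

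**Step 3. Compare with two plausible intended readings.**
- 0.10 ppm = 12.3 Hz (2.89 T) to 12.8 Hz (3.0 T). The printed limit is 10 ÷ 0.10 = 100 times wider.
- 10 Hz = 10 ÷ 123.05 = 0.081 ppm to 10 ÷ 127.73 = 0.078 ppm. The printed limit is 1,230 ÷ 10 = 123 to 1,277 ÷ 10 = 128 times wider.

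Either fits a decimal or unit slip. The two differ from each other by about a quarter, so they would not exclude the same spectra.

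**Step 4. Does the signal-to-noise limit stand in?** If a line broadens from w0 to w, the starting signal-to-noise ratio needed to remain at 10 or above is 10 × w ÷ w0.

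| Broadened to | w0 = 0.04 ppm | w0 = 0.06 ppm |
|---|---|---|
| 0.10 ppm | 25 | 16.7 |
| 0.15 ppm | 37.5 | 25 |

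A broadened spectrum whose starting ratio was at least these values passes the signal-to-noise limit. The SD limit was not quantified, because the article gives no basis for doing so.

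**The case against.** The strongest reply is that this is a printing slip in a condensed article, in a rule for exploratory data, with two working safeguards beside it. Much of that stands.

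- **The other limits still act.** A reader might infer that broadened spectra enter the analysis unchecked. The article does not support that: the signal-to-noise and SD limits each exclude on their own. The SD limit applies metabolite by metabolite and would be expected to rise as overlapping peaks become harder to separate. The share of broadened spectra that would pass both limits is unknown.
- **The primary analysis is untouched.** It consists of three correlations between change in n-back activation and change in FAST, and the sample size in section 2.2 rests on those. Nothing in either depends on this limit.
- **The effect on glutamate is narrower than it may seem.** Poor separation of glutamate from glutamine harms the glutamate estimate more than Glx, their sum, which is also fitted.
- **Practice may differ from print.** Nothing shows that the screening script carries 10 ppm.

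What does not stand is the step from minor to harmless. The unit is printed, no other section corrects it, and the sentence is a decision rule in the methods. Three limits joined by *or* imply that each was meant to exclude by itself, and one cannot. The signal-to-noise limit does not replace it, as step 4 of the working shows.

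**Conclusion.** The point holds in a limited form. As written, the linewidth criterion can exclude no fittable spectrum: 10 ppm at 3 T is about 1,230 to 1,280 Hz, or 2.0 to 3.3 times an assumed metabolite range of 3 to 5 ppm. The proton frequency and the metabolite range are assumptions, but the conclusion is the same throughout the spans used. That some broadened spectra can pass the signal-to-noise limit rests on further assumptions about good linewidth and about how peak height falls with broadening.

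The consequence is confined to the secondary, exploratory spectroscopy models. How many spectra are affected, and by how much the correlations would change, cannot be computed from the article.

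It may also be tempting to conclude that the limit should read 0.10 ppm. The article does not establish this: 10 Hz, about 0.08 ppm, is equally consistent with the slip.

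**What to change.** The sponsor should confirm the intended linewidth limit and its unit, then correct that one figure in section 2.6. The screening script should be checked to confirm that it applies the corrected value in the same unit. Both should be done before any spectra are screened, so that the limit is not chosen with the data in view.

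The cost is one figure in the text and one check of the script. A working limit may exclude some spectra that would otherwise pass, which would slightly reduce the number available for the spectroscopy models. The primary analysis and the sample size need no change.
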